## Abstract

**Background:**

Male infertility is a significant contributor to the need for fertility treatment. Treatment currently involves correcting any identifiable adverse lifestyle factors in men with suboptimal sperm parameters, and if these measures are unsuccessful, assisted conception is offered, which can be quite expensive. Raised scrotal temperature is one of the least studied but easily corrected risk factors for male infertility. In a recent review of the literature, sperm count, motility and morphology improved with scrotal cooling devices. The devices used to achieve testicular cooling were, however, not practical for day-to-day use. A potentially more practical device for scrotal cooling has recently been developed. The Babystart® FertilMate™ Scrotum Cooling Patch is a hydrogel pad which allows for comfortable application. The aims of this study were to investigate whether exposing the scrotum to lower temperatures by means of these new patches could improve semen parameters, thereby improving fertility, and to assess the feasibility of a clinical trial.

**Methods/design:**

This is a randomised controlled trial set in a university teaching hospital in the United Kingdom. The proposed sample size was 40 men with mild, moderate or severe oligoasthenospermia, of whom 20 would be randomised to wearing the scrotum cooling patch for 90 days and 20 men would be acting as controls and not wearing the patches. The primary outcome measure was the change in sperm concentration. Secondary outcome measures included the change in sperm volume, motility and morphology; endocrine parameters; metabolomic biomarkers; testicular volume and blood flow. Reasons for dropping out and non-compliance were also going to be noted and reported.

**Discussion:**

The study started recruiting in October 2011 and as of November 2011 four men had been consented and were participating in the study. No operational challenges had been encountered at the time of the submission of this manuscript. Although the study also aimed to evaluate the feasibility of a definitive study, the change in sperm count after 90 days of wearing the scrotal cooling patches was made the primary outcome measure because a statistically significant improvement in sperm parameters with the scrotal patches would in itself be a definitive finding.

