### Outcome measures

The primary outcome measure will be the change in sperm concentration after 90 days in men wearing the Babystart® FertilMate™ Scrotum Cooling Patch compared to men not wearing the scrotal cooling patch. Secondary outcome measures will include the change in sperm volume, motility and morphology. Other secondary outcome measures will include the change in endocrine parameters (testosterone, follicle stimulating hormone and luteinising hormone), metabolomics biomarkers, testicular volume and blood flow as measured on three-dimensional ultrasound. Statistical correlations between testicular volume, blood flow and metabolomics biomarkers and semen parameters will also be evaluated. The number of potentially eligible men seen at each clinic will be noted and the proportion of these who consented to the study and completed the study will also be evaluated. Reasons for dropping out and non-compliance will also be noted and reported.

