### Statistics and data-analysis

Baseline characteristics will be compared between men wearing the scrotal patches and controls by using Chi-squared tests for categorical variables and independent *t*-test for the normally distributed continuous variables. If the assumptions for normality are violated then non-parametric techniques will be applied. All statistical analyses will be conducted using SPSS or other validated statistical software and statistical significance reached when *P* <0.05 (two-tailed). Furthermore, parameter estimates will also be accompanied with 95% confidence intervals. No formal power calculation was done for this pilot study but we aim to invite sufficient eligible men to participate such that we actually recruit 20 men into each arm of the study (40 in total). This number was thought to be reasonable for estimating standard deviations of continuous variables and estimating recruitment to inform a definitive trial if required. Dichotomous data will be analysed as rates and continuous data as medians and ranges.

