## Discussion

This study addresses an important but insufficiently explored area of male fertility. The potential economic benefits lie in the fact that the use of the scrotal cooling patches could, alongside the implementation of other important lifestyle changes in men with suboptimal sperm parameters, reduce the number of men who need expensive assisted conception. The study started recruiting in October 2011 and to date (November 2011) four men have been consented and are participating in the study. We have not encountered any operational challenges so far.

The study was also set up as a feasibility study and aims to evaluate factors which would be important should a definitive study be required. These include the recruitments rates and data for a power calculation. However, as we do not quite know how marked the effect of the scrotal patches will be, we decided to make the change in sperm count after 90 days of wearing the scrotal cooling patches compared with the control group the primary outcome measure, because if statistically significant differences between groups are identified, a *post hoc* sample size calculation could show that the current sample size (20 in each arm) was of sufficient power.

There was some discussion about the need or not for placebo patches in the control group. We decided against this as the placebo patches could raise the scrotal temperatures in men wearing them, resulting in a lowering of the sperm parameters in the control group introducing bias.

We have also chosen to assess testicular blood flow in this project as some studies show that this is associated with male fertility [14]. Endocrine factors and seminal fluid metabolomic biomarkers [15] have also previously been evaluated and shown to be related to male fertility. We have therefore also used the opportunity to investigate whether changes in endocrine levels and serum metabolomic profiles, which are possible surrogate markers of male fertility, occur as a result using the scrotal cooling patches.

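### A significant result is called definitive, and a post hoc calculation is to show adequate power, although the trial is an unpowered pilot of 20 men per arm

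*Protocol article*

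**What the plan says.** The Discussion paragraph of the abstract explains why an efficacy outcome was made primary in a study that also tests feasibility: "a statistically significant improvement in sperm parameters with the scrotal patches would in itself be a definitive finding". The main Discussion gives a related reason. The size of the effect is unknown, and if the groups differ significantly, a sample size calculation done afterwards could show that 20 per arm had been enough.

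Statistics and data-analysis describes a different kind of study: "No formal power calculation was done for this pilot study". The 40 men were judged "reasonable for estimating standard deviations of continuous variables and estimating recruitment to inform a definitive trial if required". The same section sets one threshold for all analyses: "statistical significance reached when *P* <0.05 (two-tailed". It also promises 95% confidence intervals with parameter estimates.

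On the primary outcome, the Outcome measures section states: "The primary outcome measure will be the change in sperm concentration after 90 days". Volume, motility and morphology are secondary. The main Discussion words the primary differently: "we decided to make the change in sperm count after 90 days of wearing the scrotal cooling patches".

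**The concern.** The article claims for a significant result a status that its own sample size rationale does not support. In the statistics section, a definitive trial is something that this study would inform. In the abstract, this study becomes definitive itself once p falls below 0.05. The only support offered is a calculation made after the result is known, which adds no information to the p-value.

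Two consequences follow. First, a significant difference from 40 men could be reported as settling whether the patch works. Second, the main Discussion wants data for a power calculation. If the observed effect is carried forward because it was significant, it will tend to be too large, and the next trial will tend to be too small.

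**Working it through.** **Inputs from the article.** 20 men per arm; two-sided 0.05; one primary and three secondary semen outcomes; no power calculation. No effect size or SD is stated, so 40 cannot be reproduced from anything given.

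**Assumptions made here.** The primary is compared by a two-sample t-test with all 40 men analysed. The article names the t-test only for baseline comparisons and allows non-parametric methods. True effects are in SD units and are illustrative.

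**1. Smallest significant difference.** The critical t on 38 degrees of freedom is 2.024. The observed difference must be at least 2.024 × √(2/20) = 2.024 × 0.316 = 0.64 SD.

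**2. What a post hoc calculation shows.**
- Power at an observed difference of 0.64 SD (p exactly 0.05): the noncentrality is 0.64 × √(20/2) = 2.024, equal to the critical value. Power is 50% by normal approximation and 50.5% by noncentral t.
- Sample size for 80% power at that difference: 2 × (1.960 + 0.842)² / 0.64² = 15.7 / 0.41 ≈ 38.3, so 39 per arm, not 20.
- Post hoc power reaches 80% only when the observed z is 1.960 + 0.842 = 2.80, which is p ≈ 0.005.

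The answer is fixed by the p-value in every case. It cannot show that the design was adequate.

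**3. Power before the data, and inflation among significant results.** Power is by noncentral t. Inflation is the mean absolute estimate among significant results divided by the true effect, simulated with 20 per arm.

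| Assumed true effect (SD) | Power | Inflation |
|---|---|---|
| 0.2 | 9.5% | about 3.8 |
| 0.3 | 15% | about 2.6 |
| 0.5 | 34% | about 1.7 |
| 0.8 | 69% | about 1.2 |
| 1.0 | 87% | about 1.07 |

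Power of 80% needs a true effect of about 0.91 SD, before any dropout. A true 0.5 SD would need 63 per arm (normal approximation).

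**4. False-positive improvements, on each reading of the abstract.** No true effect on any outcome is assumed.
- Primary only: 2.5% in the direction of improvement.
- All four semen outcomes, each at 0.05 two-sided, independent: 1 − 0.975⁴ = 9.6%.
- All four, with assumed equal pairwise correlations of 0.3, 0.5 and 0.7 (simulated): 8.7%, 7.8% and 6.5%.

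**The case against.** The strongest defence is that the abstract's sentence gives the reason for choosing one primary outcome. A reader might infer that a significant result on any single semen parameter would be declared definitive, and so quote 1 − 0.95⁴ = 18.5% as the error rate. The documents do not support that. One primary is named, the other semen outcomes are listed as secondary, and no section says that a secondary result alone would be definitive. The 18.5% also counts significant deterioration, whereas the sentence speaks of improvement. What stands is that the plural is loose and leaves the wider reading open.

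A reader might also infer two competing primary outcomes, concentration and count. The Participants section gives count per millilitre, and no total count is defined, so the two words are probably synonyms. One name would still help, because total count is concentration times volume and volume is a separate outcome.

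Three further readings go too far:
- Unadjusted testing of secondary, hormonal or metabolomic outcomes is not a fault here. It is acceptable in a pilot with one named primary, and such handling is commonly left to the analysis plan.
- Severe inflation is not certain. It depends on a true effect that the authors say they do not know, and it is slight if the effect is large.
- The remarks on live birth are not a contradiction. The Discussion says the study cannot address it unless the effect is marked, which is a disclosed limitation.

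The authors could add that a later trial is foreseen only if required, so a large effect might make one unnecessary. A very large effect could indeed be persuasive. The stated criterion, however, is statistical significance, not size or precision.

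**Conclusion.** The concern holds in a limited form. The article claims a definitive status that its design lacks, and supports it with a post hoc argument that cannot work. This is true even if only the primary outcome was meant.

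A result just at p = 0.05 has post hoc power of about 50%. Significant estimates would be inflated about 3.8-fold at a true 0.2 SD, 1.7-fold at 0.5 SD and 1.2-fold at 0.8 SD. These figures rest on a t-test with 40 men analysed and on assumed true effects. The rise in false-positive improvements from 2.5% to about 6.5% to 9.6% is conditional on reading the abstract's plural as all four semen outcomes, with no true effects and correlations between 0 and 0.7. On the narrower reading it does not arise.

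The defect lies in what the trial may conclude, not in its conduct. Four men had joined when the article was written, so at that point it could be corrected before any results.

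**What to change.** - Delete the claim of a definitive finding from the abstract, and the post hoc sample size argument from the main Discussion.
- Restrict the efficacy test to the single primary outcome, the between-group comparison of change in sperm concentration in million/mL, and use that name and unit in every section.
- State that a significant result is preliminary evidence that needs an adequately powered trial. It should not be called confirmatory at this sample size either.
- Report volume, motility and morphology as exploratory estimates with the 95% confidence intervals already promised.
- When planning the next trial, use the SD and recruitment estimates from this one, and do not take the observed effect at face value because it was significant.

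The cost is wording only; no change to recruitment, visits or measurements is needed. The downside is that a significant result will support a weaker claim than the authors had hoped for.

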**Trial registration:**

Current Controlled Trials ISRCTN94041896

## Background

Male infertility is a significant contributor to the need for fertility treatment in the UK and approximately one-third of *in vitro* fertilisation cases are due to male factor infertility. Sperm integrity is essential for successful conception. Spermatogenesis is a very complex process and any hindrance to this vital process may result in altered sperm parameters. Many factors have been associated with male infertility and impaired spermatogenesis, including factors which can be corrected by lifestyle changes and organic factors. However, in many cases, the cause is unknown. Lifestyle factors include raised scrotal temperatures, alcohol, obesity, smoking and free radicals [1-5]. Organic causes are usually classified as pre-testicular, testicular and post-testicular. Pre-testicular causes include endocrine factors which impair spermatogenesis, such as hypogonadotrophic hypogonadism; testicular factors include diseases, such as mumps orchitis, trauma or radiation treatment in cancer patients; post-testicular factors leading to obstruction to the outflow of sperm from the epididymis to the penile urethra can occur after infection and surgery such as vasectomy.

The current approach to treating male infertility includes correcting any identifiable possible contributory adverse lifestyle factors, and if unsuccessful, assisted conception by way of intrauterine insemination and *in vitro* fertilisation and intracytoplasmic sperm injection. Assisted conception is, however, invasive and costly. There is therefore a need to improve the efficacy of non-invasive and lifestyle treatment options in male infertility.

Alcohol and smoking are personal choices which can be corrected with appropriate support and counselling. Antioxidant supplementation via carnitines and vitamins C and E can be offered to correct free radicals but further studies are needed to determine the efficacy and safety of antioxidant supplementation in the medical treatment of male infertility. Raised scrotal temperatures and heat is one of the least studied risk factors for male infertility, but one that can easily be corrected. Heat has an adverse effect on spermatogenesis and it is believed that scrotal temperatures 1 to 2°C below body temperature would be a natural advantage to normal sperm morphology [3-5]. In a review of the literature, sperm count improved in 48% to 66% of the infertile men studied and six out of eight studies also showed an improvement in sperm motility, morphology or both with scrotal cooling, ranging from 28% to 83% [5-12]. The increase in sperm count was noted as early as two weeks in oligospermic men after treatment initiation but a statistically significant increase in sperm count was noticeable from eight weeks onwards. The devices used to achieve testicular cooling were, however, not practical for day-to-day use. One device was a curved ice rubber collar filled with ice cubes that was attached to participants’ thighs using tapes on either side and was applied for 30 minutes for 14 consecutive days. A second was a gel that became solid on freezing. It was wrapped in a cloth or towel and inserted in the participants’ underwear on the anterior aspect of the scrotum every night for two months. It would thaw within three to four hours, resulting in a cooling effect. A third device comprised a cotton suspensory bandage worn for between 16 to 22 hours for a period that ranged from 8 to 20 weeks, which was held in close contact with the scrotum and released fluid (water or alcohol) to keep the scrotum damp. A final example is a device that attached with a belt to the abdomen and scrotum and released a continuous air stream to achieve scrotal cooling, which was applied nocturnally for 12 weeks.

A potentially more user friendly and practical device for scrotal cooling has recently been developed. The Babystart® FertilMate™ Scrotum Cooling Patch (Babystart Limited, Dudley, UK) is a hydrogel pad which is non- greasy and allows for comfortable application. The scrotal cooling patch contains 0.5% w/w natural I-menthol,which provides the cooling effect. The patch is easily trimmed and shaped for use on all sizes of scrotum and comes in a re-sealable bag, with no need for refrigeration. The potential benefits with the Babystart® FertilMate™ Scrotum Cooling Patch include the fact that it is easily applied, comfortable and maintains the individual’s dignity and privacy.

There have not been any previously published clinical trials evaluating the impact of the Babystart® FertilMate™ Scrotum Cooling Patch on male fertility. The aims of this study were to investigate whether exposing the scrotum to lower temperatures using this patch could improve fertility by means of improved semen parameters and to assess the feasibility of a clinical trial study.

## Methods

### Ethics approval

Local research ethics approval was obtained for this study from the Nottingham Research Ethics Committee, East Midlands - Nottingham 1. 11/EM/0163.

### Study design

The study was designed as a randomised controlled trial and no stratification will be used.

### Setting

The study is being carried out in a fertility clinic at a university teaching hospital in the UK, the Nottingham University Hospitals NHS Trust, Queens Medical Centre Campus.

### Participants

The proposed sample size is 40 men with mild, moderate or severe oligoasthenospermia, with 20 men in the experimental group using the scrotal cooling patch and 20 men in the control group and not receiving the scrotal cooling patch. The inclusion criteria include men presenting to the fertility clinic with mild, moderate or severe oligoasthenospermia (sperm motility of < 32% and count of <15 million per millilitre), aged 18 to 45 years of age. Exclusion criteria include men who have undergone a vasectomy or have had any surgery to their genitalia, have an allergy to menthol, are aged below 18 or older than 45 years of age, are unable to consent for themselves, from vulnerable groups or with a chronic medical condition, for example diabetes or hypertension.

### Recruitment and consent

Prior to each weekly fertility clinic at the Nottingham University Hospitals, Queen’s Medical Centre campus, the medical records of all couples to be seen in the clinic will be reviewed to identify any potentially eligible men for the study. Men will be approached after their clinic consultation to be provided with verbal and written information about the project. If they agree to participate, written informed consent will be obtained prior to participation by a competent individual and a signed document will be retained in their research records. The initial approach will be from a member of the patient’s usual care team, which may include the investigator. The investigator or their nominee, for example, from the research team or a member of the participant’s usual care team, will inform the participant of all aspects pertaining to participation in the study. If needed, the hospital interpreter and translator services will be available to assist with discussion of the trial, the participant information sheets and consent forms, but the consent forms and information sheets will not be available printed in other languages.

Potential participants will be told that that entry into the trial is entirely voluntary and that their treatment and care will not be affected by their decision. They will also be told that they can withdraw at any time but attempts will be made to avoid this occurrence. They will also have explained to them that, in the event of their withdrawal, their data collected so far cannot be erased and we will seek consent to use the data in the final analyses where appropriate.

### Pre-randomisation data

Baseline clinical demographics will be collected from the participant’s medical records and through a clinical interview, including age, occupation, medical history, cigarette use, alcohol intake, body mass index and a working clinical diagnosis. The results of the baseline semen analysis justifying inclusion into the study will be recorded in the research proforma and a blood sample will be collected for endocrine variables, including testosterone, follicle stimulating hormone and luteinising hormone. Serum samples will also be stored at −80°C for metabolomic biomarkers and a three-dimensional ultrasound scan of the scrotum will be performed to evaluate scrotal testicular blood flow, volume and morphology.

### Randomisation and blinding

Randomisation will be carried via a web-based programme. This will be done by accessing the assigned randomisation status on the web-based program. The web-based program currently chosen is Randomization.com [13], which is a free on-line randomisation program which prints simple lists of random allocations. Allocation concealment will be achieved by centralised randomisation. The randomisation program generates a list of 40 patients in a random sequence and as patients are recruited they are added to the list in numerical order of randomisation in line with the predetermined randomisation sequence.

The researchers performing and analysing data from the semen samples, endocrine tests, biomarker analysis and three-dimensional ultrasound scans will be blinded to the participant grouping.

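### The article claims concealment by centralised randomisation, but the process it describes is a predetermined list of 40 filled in order, with no independent holder and no release step

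*Protocol article*

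**What the plan says.** All the relevant statements on method are in the Protocol article, section Randomisation and blinding.

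- The property claimed: "Allocation concealment will be achieved by centralised randomisation".
- The tool: Randomization.com, "which is a free on-line randomisation program which prints simple lists of random allocations".
- What it produces: "The randomisation program generates a list of 40 patients in a random sequence".
- How it is used: "as patients are recruited they are added to the list in numerical order of randomisation in line with the predetermined randomisation sequence".
- How an allocation is obtained: "This will be done by accessing the assigned randomisation status on the web-based program".

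The same section blinds those who perform and analyse the semen, endocrine, biomarker and ultrasound measurements. It does not mention those who recruit.

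On recruitment, the section Recruitment and consent says "The initial approach will be from a member of the patient’s usual care team, which may include the investigator". The section Setting names one site: "The study is being carried out in a fertility clinic at a university teaching hospital in the UK". Study design rules out stratification. The Abstract gives the intended split: "20 would be randomised to wearing the scrotum cooling patch for 90 days and 20 men would be acting as controls".

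**The concern.** Concealment means that the person deciding whether to enrol a man cannot know his allocation until he is irrevocably in the trial. Central randomisation achieves this because a party outside the clinic registers the man first and only then discloses one assignment. The article uses the name of that method but describes another: a complete sequence produced at the outset and filled from the top. Such a sequence is concealed only if someone separate from recruitment keeps it and discloses one line at a time. The article describes neither.

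Several features of this trial make the gap matter:

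- Medical records are reviewed before each clinic, and the qualifying semen result is already on file, so a recruiter can know a man's severity before approaching him.
- Eligibility runs from mild to severe oligoasthenospermia, and nothing is stratified.
- There is no placebo patch, so past allocations are visible to anyone who sees the participants.
- The primary outcome is change in sperm concentration, which plausibly depends on where a man starts.

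A recruiter who knew the next allocation could, even without intent, approach or encourage different kinds of men for each arm. Blinded laboratory work would then measure two dissimilar groups accurately. With 20 men per arm, the planned baseline comparisons would have little ability to reveal it.

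**Working it through.** The plan gives no figure on this point to reproduce. The only arithmetic in it is 20 + 20 = 40, which agrees with the list length. The main check sets the claim beside the process.

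**1. Claim against process**

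| What concealment by a central system needs | What the article gives |
|---|---|
| A holder of the sequence who is separate from recruitment | None named |
| Registration of the man before disclosure | Not described; men are added to an existing list |
| Release of one allocation at a time | Not described; the tool is said to print lists |
| Upcoming allocations out of recruiters' reach | Not stated either way |

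The statement that status is accessed on the web program comes closest to a release step. It fits poorly with a tool described as printing lists, and it does not say who has access or how much of the list they see.

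**2. Order of events**

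Consent comes first (Recruitment and consent), then baseline data (Pre-randomisation data), then treatment once randomised (Interventions). That order is sound. It does not conceal a sequence that already exists before the man is approached.

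**3. Size of the risk, under two assumptions about visibility**

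*List visible to a recruiter.* Every allocation still to come is known. The Discussion says four men were participating by November 2011. If all four had been allocated, 40 − 4 = 36 allocations remain, and all 36 would be known.

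*List hidden, past allocations visible.* Assume the list is a single sequence restricted to 20:20; the article does not state this. A person who always guesses the arm with fewer men so far, with n = 20 per arm, expects

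correct guesses = n + (4^n / C(2n, n) − 1) / 2

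- 4^20 / C(40, 20) = 7.976
- 20 + (7.976 − 1) / 2 = 23.49
- 23.49 / 40 = 58.7%

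A simulation of 50,000 such lists gave 23.48 correct (58.7%), with on average about 1.9 final allocations fully determined. The benchmark with full concealment and no restriction is 20 of 40, or 50%.

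Most of the exposure therefore lies in who can see the list. The guessing that remains once a 20:20 list is properly held is modest.

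**The case against.** The strongest reply is that a predetermined sequence filled in order is compatible with concealment. A central service and a set of numbered sealed envelopes both work from one. What matters is who keeps it, and a condensed article may leave that to the full protocol. The article does say centralised, and it does say that allocations are accessed through a web program.

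Part of this stands. A reader might infer that recruiters see the list, or that the next allocation is known before consent. The article says neither. It is silent on who generates, holds or reads the list, and silence is not evidence that the clinic team has it.

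A reader might also take the description of the lists as simple to mean unrestricted randomisation, and conclude that the 20/20 split is not delivered. That is not supported either. The word may only describe the printout, and a list of 40 with 20 per arm is consistent with a balanced sequence.

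What does not stand is treating the point as a mere omission. The article names its concealment method and then describes a process that, as written, does not supply it. A fuller protocol would have to replace that description and not only add detail to it.

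**Conclusion.** The concern holds in a limited form. As described, the process does not deliver the concealment that the article claims for it. Foreknowledge by recruiters is a risk that the text leaves open; it is not shown to have occurred.

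The size depends on facts that are not given. If the list is visible, all remaining allocations are known. If it is hidden and is one 20:20 sequence, about 58.7% can be guessed from past allocations, against 50% under full concealment without restriction. No amount of bias in the treatment comparison can be derived, because the article gives no standard deviation, effect size or breakdown by severity.

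The pilot label does not remove the need for correction. The Abstract's Discussion says that a statistically significant improvement would in itself be definitive, and selective enrolment cannot be undone at analysis.

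**What to change.** Replace the sentence on centralised randomisation with a description of the mechanism:

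1. Existing staff outside screening, consent and assessment, for example in the hospital research office, generate and hold the list.
2. Each allocation is released singly, by phone or by sequentially numbered opaque sealed envelopes, and only after consent, eligibility and baseline data are recorded.
3. The text says that the list is restricted to 20:20, if that is intended.
4. The text documents how the first four men were allocated and who could see the list at that time.

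Blocks are not needed. A single 20:20 list already gives the intended split. Where past allocations are visible, small blocks are easier to guess: for known blocks of four, the same formula with n = 2 gives 2 + (16/6 − 1)/2 = 2.83 of 4, or 70.8%.

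The cost is a few hours of administration, a small amendment and a short delay between consent and allocation. No new staff are required. With up to 36 men still to be allocated, the change would protect most of the trial.
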